#### 6.4.3.2. Analyses required for the study

| ADDITIONNAL TESTS/ INFORMATIONS REQUESTED FOR THE STUDY                                                                                                                                                                             |                                                                                                                                                                                               |
|-------------------------------------------------------------------------------------------------------------------------------------------------------------------------------------------------------------------------------------|-----------------------------------------------------------------------------------------------------------------------------------------------------------------------------------------------|
| FOLLOW-UP AFTER AFMT                                                                                                                                                                                                                | MICROBIOLOGY ON FAECES                                                                                                                                                                        |
| Status at last follow-up (alive, death with cause of death; remission or relapse) until the end of the hospitalization for consolidation chemotherapy
Patient will report severe events (AB effects, fever...) to the physician. | Numbers of stools and stool consistency evaluated by Stool Bristol scale during hospitalization

C. difficile Multi-drug resistant bacteria
Pathogenic bacteria and parasites |
| BIOCHEMISTRY ON FAECES                                                                                                                                                                                                              | METAGENOMIC ANALYSIS                                                                                                                                                                          |
| Calprotectin, neopterin, zonulin, secretory IgA on faeces                                                                                                                                                                           | Genetic sequencing of bacterial genes (shotgun: all metagenome sequencing)
Diversity index of bacterial microbiota
Dysbiosis characterization                                           |
| BLOOD ANALYSIS                                                                                                                                                                                                                      |                                                                                                                                                                                               |
| Monitoring of blood immune cells                                                                                                                                                                                                    |                                                                                                                                                                                               |

Table 3: List of analyses requested for the study

The patients will be followed for assessment of study endpoints and recording adverse events that could happen after intervention until the end of the hospitalization for consolidation chemotherapy. All clinical severe events will be recorded in the CRF during any patient transfer to other site or service (Emergency care). Information of type, dose, duration of antibiotherapy, immunotherapy and chemotherapy will be given to explore the possible correlation between treatments, dysbiosis status and its severity. Relationship of adverse events to AFMT will be assigned by the investigator with the help of the data. All serious adverse reaction will be reported according to the regulatory procedure of adverse reaction declaration.

#### 6.4.3.3. Management of fecal samples

|                                                                                                         |                      |                                                                                               |
|---------------------------------------------------------------------------------------------------------|----------------------|-----------------------------------------------------------------------------------------------|
| [figure not shown]
MaaT Pharma | Protocol             | Protocol N°: MPOH02
EudraCT N° : 2015-004335-12
Version 10.0
Date : 20 November 2017 |
|                                                                                                         | ODYSSEE STUDY |                                                                                               |

|                                            |                                                                                                                                                                                                                                                              |                                   |                                                                                                                                  |                                          |
|--------------------------------------------|--------------------------------------------------------------------------------------------------------------------------------------------------------------------------------------------------------------------------------------------------------------|-----------------------------------|----------------------------------------------------------------------------------------------------------------------------------|------------------------------------------|
| Place of collection                        | Hospital / Patient's home                                                                                                                                                                                                                                    |                                   |                                                                                                                                  |                                          |
| If faeces collection at home               | The patient collects his faeces at home the day before his hospitalization and bring back the collection pot in a cooler (within 24h after collection) in order to proceed to sampling by caregivers. Faeces are kept in the collection pot and in a cooler. |                                   | Faeces collected by the patient at home in the collection pot are sent within 24h after collection to the hospital by a carrier. |                                          |
| Sampling                                   | Care giver will sample faeces for analyses with a special spoon according to the procedures provided by BIOFORTIS SAS                                                                                                                                        |                                   |                                                                                                                                  |                                          |
|                                            | Metagenomic analysis                                                                                                                                                                                                                                         | Bacteriology                      | Biochemistry                                                                                                                     | For inoculum (AFMT)                      |
| Weight of samples                          | 3 x 1g                                                                                                                                                                                                                                                       | 20- 30g                           | 20-30g of faeces                                                                                                                 | Remains of the faeces (at least 100g)    |
| Material                                   | Fecal containers                                                                                                                                                                                                                                             | Fecal container                   | Fecal container                                                                                                                  | Fecal container                          |
| Conditions of transport and delivery modes | - 80°C - Carrier                                                                                                                                                                                                                                             | 4°C- Carrier within 24h           | 4°C- Carrier within 24h                                                                                                          | Room temperature - Carrier               |
| Storage location and conditions            | Storage - 80°C
- Further analysis by sequencing platform                                                                                                                                                                                                  | Immediate analysis- BIOFORTIS SAS | Storage -80°C and further analysis – BIOFORTIS SAS                                                                               | Preparation of inocula for AFMT- ACCINOV |

*Table 4: Fecal samples management*

#### **6.4.3.4. Processing of samples**

Faeces will be collected at hospital or at patient's home. Faeces collected at patient's home will be returned to the hospital by the patient or by a special carrier.

A fecal collection pot (the same provided at hospital) and a cooler will be provided to the patient with an user manual during the consultation. The patient will collect his faeces at home the day before his hospitalization and will bring back the collection pot in order to proceed to sampling by caregivers.

Faeces and blood will be sampled by caregiver. Then, the samples will be coded, anonymized, stored and sent to the central laboratory by a carrier as described in **Appendix 5**. Samples will be conserved during all study duration, in BIOFORTIS SAS and Accinov.

|                                                                                   |                      |                                                                                               |
|-----------------------------------------------------------------------------------|----------------------|-----------------------------------------------------------------------------------------------|
| [figure not shown] | Protocol             | Protocol N°: MPOH02
EudraCT N° : 2015-004335-12
Version 10.0
Date : 20 November 2017 |
|                                                                                   | ODYSSEE STUDY |                                                                                               |

According to our central lab procedures, the faeces conservation at room temperature for 24h before sampling and a delay of maximum 48h between faeces collection and microbiological analysis are acceptable.

For the inoculum preparation, a delay of maximum 72h at room temperature between faeces collection and inoculum process has been validated, as described in the IMPD.

In case of patient's request, biological resources will be destroyed according to internal procedures of each centre.

Processing of fecal samples will be as follow (cf **Appendix 6** for analysis details):

- In BIOFORTIS SAS :

- Research of MDRB (Methicillin-resistant *Staphylococcus aureus* (MRSA), Vancomycin- and glycopeptid-resistant enterococci (VRE, GRE), Extended-spectrum- $\beta$ -lactamase (ESBLs) producing Gram-negative bacteria, carbapenemase-producing bacteria)
- Research of pathogenic bacteria (*Campylobacter sp.*, *Listeria sp.*, *Salmonella sp.*, *Shigella sp.*, *Vibrio sp.*, *Yersinia sp.*, *C. difficile*)
- Research of parasites (*Strongyloides stercoralis*, *Cryptosporidium*, *Cyclospora*, *Isospora*, *Entamoeba histolytica*, *Giardia intestinalis*, *Microsporidia*).
- Assay of fecal calprotectin, neopterin, zonulin and secretory IgA
- Storage of metagenomic samples at -80°C. All samples will be sent to a sequencing platform for metagenomic sequencing for interim analysis as per DSMB charter and final analysis at the end of the study.

- In Accinov: preparation of inocula for AFMT

Processing of blood samples (2 x 9mL tubes) in BIOFORTIS SAS will be as follow:

- Extraction of peripheral blood mononuclear cells and storage in liquid nitrogen until analysis by flow cytometry at the end of the study
- Extraction of plasma and storage in a -80°C freezer until analysis by biochemistry multiplex assays at the end of the study or during the intermediate analysis

|                                                                                                         |                      |                                                                                               |
|---------------------------------------------------------------------------------------------------------|----------------------|-----------------------------------------------------------------------------------------------|
| [figure not shown]
MaaT Pharma | Protocol             | Protocol N°: MPOH02
EudraCT N° : 2015-004335-12
Version 10.0
Date : 20 November 2017 |
|                                                                                                         | ODYSSEE STUDY |                                                                                               |

## 7. STATISTICAL CONSIDERATIONS

### 7.1. Main endpoints

#### 7.1.1. Evaluation of AFMT efficacy in dysbiosis correction

The microbiota diversity will be measured by the Simpson diversity index (S). S will be calculated at the three main times D0, D30 and D40 corresponding respectively to baseline (Sb, before antibiotherapy and chemotherapy), post-treatment (Sd, dysbiosis maximum deterioration post-antibiotherapy) and final value post-AFMT (Sf). Our hypothesis is that after an expected deterioration due to chemotherapy, the microbiota diversity should return to its baseline Sb after AFMT (thus  $Sf/Sb = 1$ ). To simplify the models, we related diversity at deterioration and final values to their ratio on baseline. In what follows, Sd and Sf denote the dimensionless ratios Sd/Sb and Sf/Sb respectively.

As Simpson index constitutes a particular way at measuring microbiota, other indexes of diversity (Shannon) and germs repartition (Bray-Curtis, Sorensen, Pearson, or Spearman indexes) will be calculated.

#### Initial Power sample

By assuming repeated measurement between Sf and the two previous S values, we assume that the correlation R (Sd, Sf) is at least  $R=0.5$ . Without an accurate estimate of the standard deviation of Sd and Sf, we will consider in this first-in-man trial that a change observed as at least half of its standard deviation should be considered as clinically meaningful as defined by Cohen's rules (84). In these conditions, a sample size of at least 30 patients should provide a power of 0.875 to detect a difference of a clinically relevant difference  $\Delta=|Sf-Sd|$ , at a one-tailed significance level of 0.05.

#### 7.1.2. Evaluation of AFMT efficacy in MDRB eradication

Based on bacterial culture and analysis of resistance gene expression by metagenomics, we will evaluate the prevalence and the quantity of MDRB before (D0), after chemotherapy/antibiotherapy (D29) and after AFMT (D40).

Prevalence of MDRB will be compared between D40 and D29 to evaluate AFMT efficacy in MDRB eradication.

---

All documentation of **MaaT Pharma** is PROPRIETARY information and may not be forwarded to third parties without prior written consent from **MaaT Pharma**. Reproductions, either in part or in whole, may not be published or copied in any manner, without the explicit written consent of **MaaT Pharma**

|                                                                                   |                      |                                                                                               |
|-----------------------------------------------------------------------------------|----------------------|-----------------------------------------------------------------------------------------------|
| [figure not shown] | Protocol             | Protocol N°: MPOH02
EudraCT N° : 2015-004335-12
Version 10.0
Date : 20 November 2017 |
|                                                                                   | ODYSSEE STUDY |                                                                                               |

Further to recruitment difficulties, the company would limit the number of cases. The following table provides the sample size needed for some beta values (from 0.1 until 0.25) and for some effect size (defined as the standardized mean difference). It is apparent that small values of effect sizes need at least 44 patients (for effect size=0.4). However, when the effect size is at least 0.6 and with a beta risk of at least 0.20, 20 patients should constitute an acceptable size.

| Effect Size | Power= | 0.1   | 0.15  | 0.20  | 0.25  |
|-------------|--------|-------|-------|-------|-------|
| 0.4         |        | 66.00 | 57.00 | 49.00 | 44.00 |
| 0.5         |        | 43.00 | 36.00 | 32.00 | 28.00 |
| 0.6         |        | 30.00 | 25.00 | 22.00 | 20.00 |
| 0.7         |        | 22.00 | 19.00 | 16.00 | 15.00 |
| 0.8         |        | 17.00 | 15.00 | 13.00 | 11.00 |
| 0.9         |        | 13.00 | 12.00 | 10.00 | 10.00 |
| 1           |        | 11.00 | 10.00 | 9.00  | 8.00  |

We conclude from this table that a sample of 20 patients might constitute an acceptable sample size for this pilot study. If necessary, an exploratory analysis can be conducted from n=12 patients to evaluate the level of the standardized mean difference.

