## 2. WORKING HYPOTHESIS AND PROPOSAL

We propose to use autologous transplantation of fecal microbiota to AML or HR MDS patients treated with intensive chemotherapy and antibiotics in order to restore the balance of their intestinal microbiome and thereby eradicate treatment-induced MDRB, infection-related complications, as well as sequelae to the gastrointestinal tract. Therefore, we propose to perform a single-arm multicentre prospective FMT trial in AML or HR MDS patients receiving intensive chemotherapy, and who are usually heavily treated with broad-spectrum antibiotics during aplasia that generate a profound status of dysbiosis. For this purpose, at the time of admission and diagnosis, patients will be requested to donate stools that will be comprehensively screened, and if deemed appropriate according to protocol criteria, conditioned and stored frozen until future processing and transplantation after aplasia completion.

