## 3. OBJECTIVES

### ➤ Co-primary objectives:

- Efficacy of AFMT in dysbiosis correction in AML or HR MDS patients undergoing chemotherapy and antibiotherapy
- Efficacy of AFMT in MDRB eradication

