#### **5.2. Exclusion criteria**

- Acute promyelocytic leukemia (AML-M3)
- Known allergy or intolerance to trehalose or maltodextrin
- Pregnancy: positive urinary or blood test in female of childbearing potential
- Severe disease with a life expectancy  $< 3$  months
- Other on-going interventional protocol that might interfere with the study
- Non eligibility for collection of autologous stools upon admission:
  - Patients refusing to consent
  - Antibiotherapy at the time of study inclusion  $\geq 4$  days
  - Concomitant or previous diagnosis of a significant inflammatory bowel disease (UC, CD) or other progressive digestive disease requesting treatment or further medical exploration

|                                                                                                         |                      |                                                                                               |
|---------------------------------------------------------------------------------------------------------|----------------------|-----------------------------------------------------------------------------------------------|
| [figure not shown]
MaaT Pharma | Protocol             | Protocol N°: MPOH02
EudraCT N° : 2015-004335-12
Version 10.0
Date : 20 November 2017 |
|                                                                                                         | ODYSSEE STUDY |                                                                                               |

- Presence of severe colitis of any etiology at the time of admission or severe digestive disorders (acute or chronic diarrhea) within 3 months preceding inclusion
- Presence of blood in faeces collected at the time of inclusion
- Patient getting a recent colonoscopy (within 3 months preceding inclusion)
- Detection of MDRB, pathogenic bacteria, parasites, norovirus and/or rotavirus during screening of autologous stool collected immediately after the inclusion visit
- Non eligibility for inoculum transplantation: persistent mucositis, colitis, or haemorrhoids, presence of blood in more than 1 patient's faeces out of 3 the week preceding the transplantation
- Non feasibility of inoculum procedure: patient refusal; technical or biological mismatch of the inoculum
- Absence of effective contraceptive method for female of childbearing potential
- Lactation
- Inability to give an informed consent

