***D29 (between D24 and D34, depending on patient’s condition) – Visit 2 – Faeces analysis for dysbiosis characterization***

After aplasia completion ,faeces and blood will be collected by caregivers within 3 days before antibiotics discontinuation (around Day 29) (**Procedures will be provided by BIOFORTIS SAS**) for biochemical assay, bacteriology (detection of MDRB and *C. difficile*), determination of dysbiosis using metagenomic analysis and analysis of blood immune cells. Detection of MDRB and/or *C. difficile* will not constitute a criterion for exclusion but will allow the measure of the potential impact of chemotherapy and antibiotherapy on the emergence of these bacteria. The patient will fulfil the EQ-5D-5L questionnaire to evaluate its gastrointestinal symptoms and its quality of life. The patient is next prepared for the following AFMT according to the procedure (**Appendix 1**).

|                                                                                                         |                      |                                                                                               |
|---------------------------------------------------------------------------------------------------------|----------------------|-----------------------------------------------------------------------------------------------|
| [figure not shown]
MaaT Pharma | Protocol             | Protocol N°: MPOH02
EudraCT N° : 2015-004335-12
Version 10.0
Date : 20 November 2017 |
|                                                                                                         | ODYSSEE STUDY |                                                                                               |

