### 7.3.2. Co-primary endpoint: MDRB eradication

The significance of the difference of prevalence between final (f), deterioration time (d) and baseline time (b) will be assessed a paired t-test. As for the main endpoint, Log transformed values will be used in case the MDRB is distributed according a Log-Normal distribution.

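### MDRB eradication is judged by the net change in prevalence from D29 to D40, which equals clearance among carriers only if no non-carrier becomes positive

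*Protocol*

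**What the plan says.** Section 3 lists as a co-primary objective "Efficacy of AFMT in MDRB eradication". Section 2 names the target: the aim is to "restore the balance of their intestinal microbiome and thereby eradicate treatment-induced MDRB". MDRB found in the baseline stool excludes the patient (section 5.2: "Detection of MDRB, pathogenic bacteria, parasites, norovirus and/or rotavirus during screening of autologous stool collected immediately after the inclusion visit"), so carriage at D29 is newly detected.

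Section 7.1.2 collects more than one measure: "we will evaluate the prevalence and the quantity of MDRB before (D0), after chemotherapy/antibiotherapy (D29) and after AFMT (D40". For efficacy it names one comparison: "Prevalence of MDRB will be compared between D40 and D29 to evaluate AFMT efficacy in MDRB eradication". Section 7.3.2 reads: "The significance of the difference of prevalence between final (f), deterioration time (d) and baseline time (b) will be assessed a paired t-test". The power table under 7.1.2 is likewise set out by prevalence before and after AFMT in 20 patients.

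MDRB at D29 neither excludes a patient nor is required for AFMT. The Visit 2 text in section 6.4.2 says that its detection "will allow the measure of the potential impact of chemotherapy and antibiotherapy on the emergence of these bacteria". Carriers and non-carriers are therefore both transplanted and both counted. No section defines eradication in a patient, restricts the comparison to D29 carriers, or separates clearance from acquisition.

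**The concern.** The objective asks how many carriers lose the organism. The fixed comparison asks how the share of positive patients changes in the whole group. The two agree only if nobody who was negative at D29 is positive at D40.

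The protocol neither assumes this nor offers data for it. It says that even the prevalence after induction is not known from consistent epidemiologic data. If some acquisition occurs, the trial can report little or no eradication when most carriers cleared. Because the protocol itself names this comparison as the measure of a co-primary objective, it is not a detail left to the SAP.

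**Working it through.** **Inputs.** n = 20 and D29 prevalence p = 0.15 to 0.20 come from section 7.1.2. Clearance c = 0.75 is an assumption. The acquisition rate a is not in the documents and is assumed below.

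**The plan's own figure.** The top cell of the MDRB power table (0.20 before, 0.01 after, 20 patients) is 0.729. It was not reproduced at n = 20; the arcsine two-sample formula at two-sided 0.05 gives 0.633. The same formula with 25 per group reproduces all 15 cells. That is a separate matter, and only the table's prevalence inputs are used here.

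**Formula.** D40 prevalence = p(1−c) + (1−p)a, so the net fall = p·c − (1−p)·a. In a paired analysis a clearance scores −1, an acquisition +1 and no change 0. The mean of these is the same net change with its sign reversed, so pairing does not remove the cancelling.

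**A rate consistent with the protocol.** Take 15–20% emergence over about 29 days, at a constant rate, carried over the roughly 10 days from AFMT to D40:
- 1 − 0.85^(10/29) = 5.4%
- 1 − 0.80^(10/29) = 7.4%

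This is about 5–7%. Using the full 11 days from D29 gives 6.0% and 8.1%.

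**Expected fall at p = 0.20, c = 0.75.** Per patient, the probability of clearing is 0.20 × 0.75 = 0.15 and of acquiring is 0.80a. Prevalence does not fall when acquisitions equal or exceed clearances among the 20 (trinomial sum). At a = 0 this is 0.85^20 = 0.039.

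| a | Net fall | No fall | of which ties | of which rises |
|---|---|---|---|---|
| 0 | 0.15 − 0 = 15 points | 4% | 4% | 0% |
| 5% | 0.15 − 0.040 = 11 points | 18% | 11% | 7% |
| 7% | 0.15 − 0.056 = 9.4 points | 24% | 13% | 11% |

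The 4% arises without any acquisition, so only the excess over it is due to the choice of measure.

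**Effect on the planned test.** With complete clearance at p = 0.20, simulated power of the paired t-test (one-sided 0.05, an assumption because no level is stated for MDRB) is 0.79 with no acquisition and 0.44 at 5%. The planning value of 0.01 after AFMT cannot be reached, even with complete clearance, once a exceeds 0.01/0.80 = 1.25%.

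**What a carrier-based result would look like.** Expected carriers are 20 × 0.15 = 3 to 20 × 0.20 = 4. The chance of two or fewer is 40% at 0.15 and 21% at 0.20. Exact 95% CIs are 40–100% for 4/4 and 19–99% for 3/4.

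**The case against.** **Acquisition may be small.** AFMT follows the end of antibiotics and aplasia, the patient is then discharged, and D40 stool is taken before consolidation starts (section 6.4.2). Much of the interval is therefore planned outside hospital and off antibiotics. This stands, and it limits the size. A reader might infer acquisition of 10–15%, at which prevalence fails to fall in about 34–48% of trials. The protocol's figures do not support that, since it would mean faster acquisition after antibiotics stop than during induction.

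**Net carriage is a legitimate target.** Section 7.2.2 speaks of MDRB reduction, and patients newly colonised after AFMT bear on that. A reader might infer that non-carriers can only add noise, but they do inform the net question. They do not inform eradication.

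**Classes may be analysed separately.** A reader might infer that a patient who loses one resistant class and gains another must count as unchanged. No section says MDRB is analysed only as any versus none. Quantity is also measured and the classes are tested separately (Appendix 6), so that inference is not established.

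**The carrier-based measure has its own bias.** It conditions on a positive D29 test, and a carrier missed at D40 counts as cleared. Prevalence at equal test sensitivity does not favour D40 in this way. With 3–4 carriers this is a real drawback and a reason to keep prevalence beside it.

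**Little depends on it.** The protocol admits low MDRB power, groups MDRB with secondary endpoints in its sample-size conclusion, and calls the study exploratory. That lowers the stakes, but MDRB eradication remains a stated co-primary objective.

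**Conclusion.** The point holds. Sections 7.1.2 and 7.3.2 measure net change in carriage and call it eradication; the two coincide only if no D29 non-carrier is positive at D40.

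Under the assumed 5–7% acquisition, with 20% carriers and 75% clearance, the expected fall shrinks from 15 to between 11 and 9 points. The chance of seeing no fall rises from 4% to about 18–24%, many of those trials being ties. These sizes rest on the constant-rate assumption and on planning prevalences that the protocol does not claim to know. If acquisition is in fact nil, the fall is simply the number cleared divided by 20, and no harm results.

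A reader might infer that prevalence should be dropped. That does not follow: it answers the net question and does not depend on 3 or 4 carriers alone. What is unsupported is a conclusion on eradication drawn from it alone.

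**What to change.** In sections 7.1.2 and 7.3.2:
- Report the paired D29-by-D40 table of MDRB status.
- State the eradication result as the number of D29 carriers negative at D40 over the number of D29 carriers, with an exact 95% CI.
- Report acquisitions among D29 non-carriers separately, by organism class where classes are tested separately.
- Keep the prevalence change beside these as the net measure, and do not conclude on eradication from net prevalence alone.
- State as a limitation that a carrier missed by the D40 test counts as cleared.

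The cost is wording only, because the D29 and D40 stool tests are already planned. The price is visible imprecision: the eradication figure becomes descriptive, with an interval as wide as 40–100% even if all four of four carriers clear.
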